### Safety assessment

3.14

The participants are instructed to report any adverse events which may occur while taking the interventions. All possible adverse events will be described in the CRF. The investigator will withdraw any participant experiencing a serious adverse event. This will be reported to the MFDS within 15 working days of withdrawal according to the Korea Good Clinical Practice (KGCP) guidelines. Participants who have withdrawn will receive appropriate treatment. The investigator will have full responsibility for the safety of participants. For safety assessments, a liver function test, blood cell count test, physical examination, and urine analysis will be conducted at baseline and at visit 5. Any loss caused by the trial will be reimbursed via insurance. The safety datasets will include the participants who are administered DSHT, CST, or placebo at least once. The incidences of physical examination and self-reported adverse events will be compared using a chi-square test. A liver function test, blood cell count test, and urine analysis will be compared between the groups. The data will be categorized into either normal or abnormal groups according to their respective normal ranges. Differences between the groups will be assessed via a chi-square test.

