## Study objectives

3

The main objective is to evaluate the efficacy and safety of DSHT and CST on obese Korean women with high risk for metabolic syndrome.

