### Sample size

3.5

This trial is a pilot study to examine the feasibility of a full randomized controlled trial for evaluating the efficacy and safety of DSHT and CST in obesity and to determine the effect size for further large-scale studies. A sample cohort comprising of 120 patients have been considered after assessing their frequency of clinic visits, availability of study staff, funding availability, and dropout rates at each participating site.

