## Discussion

4

This multi-center, randomized, 3-arm placebo-controlled study is to investigate the efficacy and safety of DSHT and CST in female obese patients with high risk for metabolic syndrome. Findings from preclinical experiments have demonstrated the anti-obesity effects of DSHT in the presence of high glucose levels^[7]^ and CST has proved effective in increasing HDL levels. However, no previous clinical trials have reported their effects in obese patients with concomitant obesity-related diseases. Traditional herbal medicines are used widely in clinical practice for weight management in East Asia including Korea, but their use is contentious owing to the lack of high-quality scientifically-based evidence.^[14]^ Building on our study with evidence-based obesity treatment strategy for obese female patients with high risk for metabolic syndrome, this study may be the first to examine the efficacy and safety of DSHT and CST on in obese patients with high risk for metabolic syndrome.

There will be several limitations in this study. First of all, although we will obtain participants’ agreement on low calorie diet during the study period, daily food intake will not be fully controlled. Thus, participants will be encouraged to check their daily calorie intake before the clinic visits through continuous patient–researcher communication. Second, a short-term drug administration period has been applied, with small number of participants; thus, a larger, long-term trial is warranted to understand the impact on long-term weight and fat management.

In conclusion, this pilot study will provide support for the design and methods and determining the feasibility of the larger clinical trial among obese female patients in Korea. If the trial medicines are proven safe and efficacious, this study's findings will be used as an evidence for the use of DSHT and CST in female obesity treatment in Korean medicine clinics and hospitals.

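### With about 40 women per arm, the chi-square tests named for safety cannot support the Discussion's prospect of the products being proven safe; report risk differences with confidence intervals and tie the safety wording to them

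*Protocol article*

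**What the plan says.** All references are to the protocol article.

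- **Study objectives (section 3):** "The main objective is to evaluate the efficacy and safety of DSHT and CST on obese Korean women". Safety stands beside efficacy.
- **Safety assessment (3.14), adverse events and physical examination:** "The incidences of physical examination and self-reported adverse events will be compared using a chi-square test".
- **Safety assessment (3.14), laboratory tests:** liver function, blood count and urine results are classed as normal or abnormal, and then "Differences between the groups will be assessed via a chi-square test".
- **Sample size (3.5):** "This trial is a pilot study to examine the feasibility of a full randomized controlled trial". The number rests on logistics: "A sample cohort comprising of 120 patients have been considered after assessing their frequency of clinic visits, availability of study staff, funding availability", together with dropout at each site. No event rate, alpha or power is given for safety.
- **Randomization and blinding (3.6):** three groups, allocated 1:1:1.
- **Discussion (section 4):** "If the trial medicines are proven safe and efficacious, this study's findings will be used as an evidence for the use of DSHT and CST". The setting named for that use is Korean medicine clinics and hospitals.

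**The concern.** The chi-square test is the only between-group safety comparison that the article names. It asks whether equal incidence can be rejected. It does not ask how much excess harm the data rule out, and a conclusion that a product is safe needs an answer to that second question. In a small trial, failing to reject equality is a common result even when a product materially raises the event rate.

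The Discussion foresees a safety conclusion firm enough to serve as evidence for routine use, but the stated comparison cannot supply it. At stake is a report of no significant difference in adverse events being carried forward as support for two herbal products, when the same counts would show that a sizeable excess risk remains possible.

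**Working it through.** The article contains no power or precision calculation for safety, so there is no figure of its own to reproduce. The check asks what a non-significant result can mean at the planned size.

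**Inputs from the article.** Total 120 (3.5) at 1:1:1 (3.6): 120 / 3 = 40 per arm. The safety set is everyone who takes at least one dose (3.14), so 40 per arm is about the most available.

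**Assumptions, not in the article.** Two-sided alpha 0.05; uncorrected Pearson chi-square; one product against placebo; event rates as listed.

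**1. Probability of missing a true increase.** With counts x and y in two arms of n = 40 and pooled rate p = (x + y)/80, the statistic is (x - y)² / [80 p (1 - p)], significant above 3.84. Summing the two binomial probabilities over all non-significant pairs (x, y) gives:

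| Placebo vs product | Missed |
|---|---|
| 5% vs 10% | 85% |
| 5% vs 15% | 65% |
| 10% vs 20% | 75% |
| 10% vs 25% | 56% |
| 10% vs 30% | 37% |
| 20% vs 40% | 50% |
| 30% vs 60% | 20% |

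Variants for 10% vs 20%:
- The normal approximation gives 23.7% power, a 76% miss rate.
- Fisher's test misses 84% and the Yates-corrected test 87%.
- A three-arm chi-square on 2 degrees of freedom misses 76% if one product doubles the rate and 79% if both do.
- A one-sided test at 0.05 misses 65%.
- With 32 per arm (assumed 20% loss), the uncorrected test misses 80%.

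For scale, 80% power for 10% vs 20% would need 199 per arm. At 40 per arm with 10% on placebo, 80% power is reached only at about 36% on the product.

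**2. What a non-significant result leaves open.** Suppose 10/40 on a product and 4/40 on placebo. Then p = 14/80 = 0.175, and the statistic is 36 / (80 × 0.175 × 0.825) = 36 / 11.55 = 3.12, P = 0.077. That is not significant, yet the Newcombe 95% interval for the excess is -1.9 to +31.4 percentage points.

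**3. Equal observed rates.** Suppose 4/40 in both arms. The Wilson 95% limits for 10% are 3.96% and 23.05%. Newcombe's limits for the difference are ±√[(10 - 3.96)² + (23.05 - 10)²] = ±√(36.5 + 170.3) = ±14.4 points. A true excess of 10 points, which is a doubling from 10%, lies well inside.

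**4. No events of a given type.** With 0/40, the exact upper limit is 1 - 0.025^(1/40) = 8.8% (two-sided 95%), or 1 - 0.05^(1/40) = 7.2% (one-sided).

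**The case against.** The strongest reply has four parts.

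*The decision rule is inferred.* A reader might infer that non-significance will be read as safety. Section 3.14 does not say so, and the conditional sentence in the Discussion sets no criterion. This stands. The point is limited to the fact that the one comparison named cannot carry the conclusion foreseen.

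*Safety is not judged by chi-square alone.* A reader might infer that it is. Safety outcomes (3.11) has vital signs, examinations, laboratory results and adverse events documented, and 3.14 handles serious events individually through withdrawal and reporting to the authority. Comparing incidences also implies counts per arm. This stands too: chi-square is the only between-group comparison named, not the only safety evaluation. Individual handling protects participants but gives no basis for a comparative safety conclusion.

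*It is a declared pilot, and intervals may be in the full protocol or analysis plan.* Low power for harms is normal in a pilot and is no error here. Intervals may well be specified elsewhere, and their absence from an article is not the complaint. What remains is on the page: a fixed test and a foreseen conclusion that outruns it. The Discussion does admit the small sample, but the larger trial it calls for concerns long-term weight and fat management, and the conclusion about proven safety follows in the next paragraph.

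*The miss rate depends on chosen inputs.* It does. It would be wrong to say that a harmful product goes undetected most of the time in general: at 10% vs 30% the test misses 37%, and at 30% vs 60% about 20%. The interval argument in steps 2 to 4 does not rely on an assumed true event rate or on power, though its example counts are illustrative.

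**Conclusion.** The concern holds as a mismatch between method and conclusion. With about 40 women per arm, a non-significant chi-square cannot support a statement that either product has been proven safe. Its size: a true 10% vs 20% is missed about 75% of the time, with a range of about 20% to 85% over the rates tried, and equal observed counts of 4/40 leave roughly -14 to +14 percentage points open. The miss rates rest on assumed event rates, two-sided alpha 0.05 and an uncorrected pairwise test. The documents do not support the stronger readings that the trial is at fault for being too small or that it commits itself to equating non-significance with safety.

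**What to change.** **Safety assessment (3.14).** For each product versus placebo, report the number and percentage of women with adverse events, physical-examination abnormalities and laboratory abnormalities, with the risk difference and its 95% confidence interval (Newcombe or exact). Where an arm has no event of a given type, give the exact upper 95% limit. Keep the chi-square p values, if wanted, as descriptive, and add a sentence that a non-significant test will not be interpreted as evidence of safety.

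**Discussion (section 4).** Replace the statement about proven safety with wording tied to the upper confidence limits, for example that excess adverse-event risks above the observed upper limit are excluded.

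**Cost.** Wording and a few extra columns in the safety tables, from counts already being collected. No more patients or visits are needed. The downside is a weaker safety claim than the one now foreseen.

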### Exclusion criteria

3.3

Criteria for exclusion of participants are as follows:

1.Patients with endocrine diseases such as hypothyroidism, Cushing syndrome, etc, which can affect the weight readings.2.Patients with cardiovascular diseases, such as, heart failure, angina pectoris, myocardial infarction, and stroke.3.Patients with uncontrolled hypertension with SBP >145 mmHg or DBP >95 mmHg.4.Patients with severe renal or liver impairment (serum creatinine [SCr] > 2.0 mg/dL or 2.5 times higher than the maximum values of alanine transaminase [ALT], aspartate aminotransferase [AST], and alkaline phosphatase [ALP] in patients with normal renal and liver function.).5.Patients with a surgical history for weight reduction such as bariatric surgery.6.Patients with history of or current eating disorder such as anorexia nervosa or bulimia nervosa.7.Patients who have experienced a 10% weight reduction within the past 6 months.8.Those who decided to stop smoking within the last 3 months or who have an irregular smoking habit.9.Patients with cholelithiasis.10.Patients with narrow angle glaucoma.11.Patients receiving treatment with controlled substances including antidepressants, antiserotonins, barbiturates, antipsychotics, Central nervous system stimulants.12.Patients on any medications that may have an effect on absorption, metabolism, and excretion of drugs and weight within the last 3 months; these include appetite suppressants, laxatives, oral steroids, thyroid hormone, amphetamine, cyproheptadine, and phenothiazine.13.Patients who are in the childbearing age and do not agree to use effective contraceptive methods during the study period.14.Patients who have participated in any clinical trial within the past month.15.Patients judged unable to follow instructions of the trial by clinical trial investigators.

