### Safety outcomes

3.11

All variables related to the safety assessment of the study such as vital signs, physical examination, and various laboratory test results, including hematologic test, biochemical test, and urine test, as well as adverse events will be documented on the case report form (CRF) at every visit.

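### The planned laboratory comparison (normal or abnormal, with no baseline reference or grade) cannot show worsening in participants who are already abnormal at entry, and the entry criteria admit such participants

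*Protocol article*

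**What the plan says.** Section 3.14 (Safety assessment) of the protocol article fixes both the coding and the test for laboratory safety.

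- Scope: "A liver function test, blood cell count test, and urine analysis will be compared between the groups".
- Coding: "The data will be categorized into either normal or abnormal groups according to their respective normal ranges".
- Test: "Differences between the groups will be assessed via a chi-square test".
- Timing: the section ends its list of assessments with "urine analysis will be conducted at baseline and at visit 5".

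It mentions no change from baseline, shift, grade, or multiple of the upper limit of normal.

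Section 3.3 (Exclusion criteria) sets the liver-enzyme limit for entry at values "2.5 times higher than the maximum values of alanine transaminase [ALT], aspartate aminotransferase [AST], and alkaline phosphatase [ALP" (the sentence goes on to define the reference as people with normal function). Lower elevations do not exclude.

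For adverse events, section 3.14 says "All possible adverse events will be described in the CRF", but the between-group test is narrower: "The incidences of physical examination and self-reported adverse events will be compared using a chi-square test".

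**The concern.** Each laboratory result is reduced to one bit, defined by the reference range alone. A participant who enters above the range and rises much further has the same code before and after, and so looks identical to a participant whose raised value stayed put. The entry criteria make this possible by design for liver enzymes.

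The tested adverse-event comparison does not clearly close the gap. It covers physical-examination findings and events that participants report themselves, and a symptom-free enzyme rise is neither.

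Safety is part of the main objective in section 3, and the Discussion says the findings will serve as evidence for clinic use if the medicines prove safe and efficacious. A laboratory comparison that can show no difference while one arm worsens is weak support for that use.

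**Working it through.** The document gives no event rate, alpha or power for laboratory safety, and section 3.5 sets the total of 120 on feasibility. There is therefore no stated figure to reproduce. The check has a logical part and an illustrative part.

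**Inputs from the document.** Total 120 (section 3.5) and allocation 1:1:1 (section 3.6), so 120 / 3 = 40 per arm. Binary coding and chi-square test (section 3.14). Entry allowed above normal up to the 2.5-times limit (section 3.3).

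**Assumptions, not in the document.** Share abnormal at baseline b, the same in each arm, from 0 to 40%. Worsening w in 20% on active and 2% on placebo, unrelated to baseline status. Nobody abnormal at baseline returns to normal. Two-sided 0.05, one active arm against placebo, uncorrected Pearson chi-square.

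**Step 1: what the coding can see.** Take an assumed case with 8 of 40 abnormal at baseline in each arm. All 8 in one active arm worsen (say from 2 to 5 times the upper limit) and none on placebo do. No one else changes.

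- Planned coding at visit 5: 8/40 against 8/40, chi-square 0.00, p = 1.00.
- Coded as worsening from baseline: 8/40 against 0/40, chi-square = 80 × (8×40 − 0×32)² / (40 × 40 × 8 × 72) = 8.89, p = 0.003.

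This blindness follows from the coding. It holds whether visit-5 status or a normal-to-abnormal shift is compared, because neither separates abnormal from more abnormal.

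**Step 2: dilution, if visit-5 status alone is compared.** The proportion abnormal at visit 5 is p = b + (1 − b)w, so the difference between arms shrinks to (1 − b)(0.20 − 0.02) while the background rate rises. At b = 20%, active is 0.20 + 0.80 × 0.20 = 0.360 and placebo is 0.20 + 0.80 × 0.02 = 0.216. The difference is 0.144 instead of 0.180.

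Power was obtained by summing the binomial probabilities of all 41 × 41 possible tables in which the chi-square test rejects:

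| Abnormal at baseline | Visit-5 abnormal, active / placebo | Power, visit-5 status | Power, worsening from baseline |
|---|---|---|---|
| 0% | 0.200 / 0.020 | 0.83 | 0.83 |
| 5% | 0.240 / 0.069 | 0.60 | 0.83 |
| 10% | 0.280 / 0.118 | 0.45 | 0.83 |
| 20% | 0.360 / 0.216 | 0.29 | 0.83 |
| 30% | 0.440 / 0.314 | 0.21 | 0.83 |
| 40% | 0.520 / 0.412 | 0.18 | 0.83 |

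With a smaller effect, 15% against 2%, visit-5 status gives 0.18, 0.13 and 0.12 at 20, 30 and 40% abnormal at baseline, against 0.63 for worsening from baseline.

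Both power columns use the same test and the same 40 per arm, so the gap comes from the coding alone.

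**The case against.** **The article is condensed.** Detail on shifts or grades may sit in the full protocol or analysis plan. This stands in part. The text has tests done at baseline and visit 5 and compared between groups, without saying that visit-5 status alone is compared. A normal-to-abnormal shift would fit the wording and would remove the dilution in step 2. It would not remove the blindness in step 1, because the article itself chooses the binary coding.

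**The entry limit is a ceiling, not a prevalence.** This stands. If few participants enter with raised tests, little is lost: at 0% the two codings agree, and at 5% power on visit-5 status is still 0.60. Normalisation during treatment is also assumed away.

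**A reader might infer that worsening cannot register anywhere.** The document does not support that. All possible adverse events go into the CRF, section 3.11 has laboratory results documented there, and section 3.4 allows withdrawal when a pre-existing disease worsens. The defect is confined to the planned laboratory comparison.

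**A reader might infer that chi-square itself is unsound here,** because expected counts fall below 5 when incidence is under 12.5% (5/40). Exact calculation at 40 per arm does not bear this out: the type I error is 0.7% at 2% incidence, 4.3% at 5%, 5.9% at 10% and 5.6% at 12.5%. Fisher's exact test would cut power on the worsening endpoint from 0.83 to 0.64.

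**A reader might add that vital signs are collected but not listed among the comparisons.** Section 3.11 does name "All variables related to the safety assessment of the study such as vital signs, physical examination, and various laboratory test results", but an article may leave that analysis to the full document, so it is no finding.

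**Conclusion.** The point holds for the planned laboratory comparison and should be corrected. With a normal/abnormal code, no baseline reference and no grade, worsening in a participant already abnormal at entry cannot show, and section 3.3 admits such participants. This part needs no numerical assumption beyond reading the entry limit as 2.5 times the upper limit of normal; a more literal reading of the wording (3.5 times) would widen it.

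The dilution is conditional on visit-5 status alone being compared. Its size depends on an unstated baseline share: under the assumptions above, power drops from 0.83 to between 0.60 (5% abnormal at baseline) and 0.18 (40%). These figures illustrate the mechanism and do not predict the trial's result.

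**What to change.** In section 3.14, replace the status comparison with a treatment-emergent one. A result counts if it was normal at baseline and is out of range afterwards, or was out of range at baseline and is worse by a pre-specified multiple of baseline or of the upper limit. The investigators should set that threshold before unblinding.

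Compare each active arm with placebo, keep the chi-square test, and give the risk difference with its confidence interval. Add a baseline-adjusted analysis (ANCOVA) of log ALT and log AST, which uses the size of the change and needs no threshold.

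The same edit should reconcile the timing, since section 3.11 has laboratory results documented at every visit and section 3.14 names baseline and visit 5; this decides which values count as post-baseline.

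The baseline and visit-5 values are already collected. The cost is some wording, a few extra tables and one threshold fixed in advance.

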### Data and safety monitoring

3.15

The ISEE will monitor the clinical trial. The monitoring will begin once the first participants complete the required number of visits. All investigational institutions will be monitored based on the SOPs while this trial is in process. Auditing is not scheduled for the present study. To improve data quality, range checks for data values and double data entry will be conducted. Any other committee such as a coordinating center, steering committee, or endpoint adjudication committee will not be applicable to the present study.

### Ethics and dissemination

3.16

This trial is conducted to comply with the Declaration of Helsinki 2008 and/or the regulations of the GCP principles in the Korean MFDS. This trial has received the approval of the institutional review boards (IRBs) of all three institutions: Gachon University Gil Korean Medical Hospital (15–102), Dongguk University Ilsan Oriental Hospital (2015–07), and Sangji University Oriental Medical Center (SJ IRB 120607). The current protocol is version 1.5, and it is developed according to the SPIRIT checklist (see Additional file 1). When important protocol changes occur, the changes must be approved by the IRBs before implementation. All items have been drawn from the World Health Organization (WHO) Trial Registration Data Set. Written informed consent will be obtained prior to the study by the investigator (see Additional file 2). Moreover, we have contracted liability insurance for patient safety. The confidentiality of personal information will be ensured. Each participant will be assigned a trial identification number at enrolment. For the duration of the entire trial, data will be handled based on the trial identification number. All records will remain secure in a locked cabinet or password-protected computer files, both for the duration of the trial and after the trial has concluded. Only investigators will retain the right to access the data. The results of the study will be disseminated through scientific journals or scientific conference presentations. So far, no public access to the full protocol, participant-level datasets, or statistical code is planned.

